## **S1 Appendix. Study Protocol for Ethics Application**

### **EFFECT OF UPPER LIMB ISOMETRIC TRAINING ON HAMSTRING STRENGTH IN EARLY POSTOPERATIVE ANTERIOR CRUCIATE LIGAMENT RECONSTRUCTION PATIENTS: A RANDOMISED CONTROLLED TRIAL**

#### **Abstract**

This study aims to investigate the effects of upper limb isometric training (ULIT) combined with standard care of an anterior cruciate ligament reconstruction (ACLR) rehabilitation program on hamstring strength and physical function in the early-phase postoperative period. Early recovery of hamstring strength is critical for knee stability and functional rehabilitation post-ACL surgery. Hamstring strength deficits are prolonged issues in rehabilitation, with significant hamstring strength deficiencies in an early postoperative ACLR, especially using hamstring autograft, leading to functional limitations and an increased risk of secondary injuries. High knee muscle strength imbalances can hinder strength return in later stages. However, swelling, donor site pain, joint stiffness, and graft protection often neglect the direct activation of the hamstring in the early period. Also, clinical practice guidelines and consensus on early rehabilitation strategies are conflicting. While lower limb strengthening exercises are the mainstay of rehabilitation, this study explores the potential benefits of ULIT in promoting hamstring activation through the inter-limb posterior myofascial kinetic chain. This study hypothesise that participants receiving ULIT in addition to standard care will demonstrate better hamstring strength at 12 weeks post-operatively compared to those receiving standard care rehabilitation alone. A total of 32 patients who underwent ACLR with hamstring tendon autografts will be randomly assigned to either the ULIT group or a control group. The ULIT group performed upper limb isometric exercises in addition to standard postoperative rehabilitation, while the control group followed the standard rehabilitation protocol alone. We will measure hamstring and quadriceps strength using hand-held dynamometry at baseline (preoperative), 4, 8, and 12 weeks postoperatively. The primary outcome is the change in hamstring strength in the operated limb, while secondary outcomes included hamstring flexibility and patient-reported outcomes on symptoms, physical function and adherence. Statistical analysis will be conducted to compare the strength recovery between the two groups. It is believed that the results of this study will enhance knowledge about the global functional muscle concept, offer effective, safe, inexpensive, and feasible interventions, and promote further research on the interlimb connection of muscle activation and flexibility in heterologous muscle groups after ACLR.

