## **Study Design**

This is a longitudinal, parallel-group, concealed allocation, randomised (1:1) controlled, single-blinded (assessor) study conducted at a tertiary hospital. If participants satisfy the eligibility criteria, provide informed consent, and have completed baseline measurement testing, they will be randomly assigned to the study. Participants will be informed that they will be randomly

assigned to one of two study groups: 1) the intervention group (ULIT plus standard care ACLR rehabilitation protocol) or 2) the control group (standard care rehabilitation protocol).

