### **Inclusion/Exclusion Criteria**

The inclusion criteria are as follows: individuals who plan for ACLR using a ipsilateral hamstring tendon autograft, with or without a meniscal injury, capable of understanding English and giving informed consent, and are aged between 18 to 45 years. The following factors are considered as exclusions: Individuals with a revision ACL surgery, a multi-ligament injury (such as instability in the collateral, posterolateral, medial, or posterior cruciate ligaments), the use of allografts, an upper limb and contralateral lower limb injury after ACL surgery.

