## **Randomisation and Allocation**

Following the baseline assessments, individuals will be assigned either to the intervention group or the control group by a simple random sampling. The randomisation process will be performed using a computer-generated sequence numbering scheme ranging from one (1) to thirty-two (32), with an equal allocation ratio of 1:1. The concealment is achieved using a set of sealed and numbered envelopes. Allocation takes place following baseline testing (T1), when a staff of the Orthopaedic Department, who is not participating in the study, opens the next study envelope. Subsequently, they notify the group assignment to the attending physiotherapist. The envelopes will be securely stored and sealed in a cabinet to ensure security and prevent any unauthorised access. Measures will be implemented to restrict the number of authorised individuals who have access or authority to open the research envelopes, to prevent any potential bias in the allocation process. The statistical analysis will specifically focus on allocation codes, ensuring that the data analyzers remain unaware of the study group allocation (see Figure 9).

[figure not shown]

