### **Intervention Group (ULIT + Standard Care)**

A single physiotherapist will administer the ULIT. The treating physiotherapist will present the ULIT to patients in verbal, demonstration, and written formats. In the fourth week following ACLR surgery, the treating physiotherapist will conduct the ULIT as a single, personalised session. The treating physiotherapist will instruct patients to follow the ULIT from 4 to 12 weeks post-operatively together with the standard care ACLR rehabilitation protocol. The ULIT comprised three concise isometric exercises: 1) wall push-up, 2) shoulder extension, and 3) shoulder external rotation (see Appendix I). The intervention group will be instructed to continue the ULIT plus standard care rehabilitation daily as a warm-up and home exercise programme for eight weeks.

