### **Blinding**

The individuals responsible for evaluating the results and managing the data are unaware of the assigned therapy. Participants will be informed that they will be assigned randomly to either the standard care group or the intervention group. The patients are reminded not to reveal their group allocation to the physician or medical officer who performed the outcome assessment. The details of ULIT are not recorded in the medical record. A sports physician and medical officer, who is blinded to the group allocation and located away from the physiotherapy outpatient unit, will assess all outcome measures at the Orthopaedic Clinic. If any participant notifies the assessor about their post-operative training session, this information will be

recorded and reported. The rationale for this notification will be documented when the randomization is revealed. An intention-to-treat analysis will be conducted.

Due to the nature of the treatments, it will not be possible for physiotherapists to be blinded to the treatment allocation of patients. The primary investigator (PI) and data analyst (not from the same departments) will be unaware of the treatment allocation as data will be evaluated using coded identification numbers. The central study coordinator (a staff who is not involved in intervention and outcome assessment) will be responsible for coding and re-coding the identification numbers.

A half-day training workshop for blinded assessors and treating physiotherapists will be conducted before this study commences to enhance data quality and protocol adherence, reduce the bias risk of assessment and treatment, and increase the confidence and competence of the investigator.

To assure the overall standard and credibility of this clinical study, the process of disclosing the assigned treatment to participants will only be done in exceptional instances, for instance when there is a risk of harm, and when knowing the real treatment becomes essential for the participant's ongoing care. Before disclosing the group allocation, the PI will determine the necessity and amount of un-blinding. The allocation will remain confidential and will not be revealed to other study team members. If any code breaks occur, the PI will report it with the justifications.

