### **Data Collection**

The study will collect demographic data, as well as pre-, intra-, and postoperative data (see Table 3). Data will be gathered from the participants and their medical records for all the data collection forms (see Appendix A, C, and D). Baseline evaluations will be conducted throughout the pre-operative period, within a range of 14 days, to reduce any bias when selecting participants. The subsequent assessment in the 4th week ( $\pm 14$  days), 8 weeks ( $\pm 14$  days), and three months ( $\pm 14$  days) are scheduled at the Orthopaedic Clinic (van Melick et al., 2021). The blinded assessors will give all tests and questionnaires in person, ensuring participant consistency. These assessments will take place at four weeks, eight weeks and three months after the surgery. Phone consultations will be used for post-hospital discharge follow-up. Participants who cannot be reached by phone for a continuous period of 14 days starting from the assessment due date will be classified as lost to follow-up for outcome measurement.

intra-reliability had a value of 0.9269 [95% C.I.: 0.8909–0.9533] (Grgic et al., 2020; Karagiannopoulos et al., 2022; Romero-Franco et al., 2019).

The participants are directed to generate deliberate isometric contractions of their quadriceps or hamstring muscles, by pushing against the resistance provided by the dynamometer's arm with a perceived maximal effort of 100% (Grgic et al., 2020). During the formal testing, the participants conducted three maximum voluntary isometric contractions (MVIC) of knee extension lasting five seconds each for the quadriceps (Padulo et al., 2020). Similarly, This is followed by knee flexion testing for the hamstrings. A minute rest time will be given between the quadriceps and hamstring testing (Mellemkjær et al., 2024).

The assessor will consistently give instruction and verbal encouragement (see Appendix I). The participants are instructed to exert maximum force by either pushing with their quadriceps or pulling with their hamstrings against the dynamometer. The average and best scores of the peak forces will be recorded (Grgic et al., 2020).

The average scores of quadriceps and hamstring muscular strength during rehabilitation are quantified using the Quadriceps Index (QI) and Hamstring Index (HI), which are calculated using the formula:  $(\text{MVIC peak force of the affected limb} / \text{MVIC peak force of the unaffected limb}) \times 100$  (van Melick et al., 2021).

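### The exclusion for limb injury after surgery can be met only by patients already randomised, which conflicts with the promised intention-to-treat analysis

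*Protocol*

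**What the plan says.** Inclusion/Exclusion Criteria names, among the exclusions, "an upper limb and contralateral lower limb injury after ACL surgery".

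The timing of allocation is spread over three sections. Study Design says that once patients are eligible, have consented and "have completed baseline measurement testing, they will be randomly assigned to the study". Randomisation and Allocation says "Allocation takes place following baseline testing (T1", when an uninvolved staff member opens the next envelope. Data Collection fixes when that baseline is: "Baseline evaluations will be conducted throughout the pre-operative period, within a range of 14 days". The Abstract also calls baseline preoperative, but it describes the randomised patients differently: "A total of 32 patients who underwent ACLR with hamstring tendon autografts will be randomly assigned".

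ULIT itself begins later: "In the fourth week following ACLR surgery, the treating physiotherapist will conduct the ULIT as a single, personalised session". It then continues to week 12.

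On the analysis set, Blinding states "An intention-to-treat analysis will be conducted". Intervention Fidelity makes the same commitment in order to protect the randomisation, and Statistical Analysis refers to the groups as randomly allocated. Withdrawal from Trial deals with patients who withdraw consent and keeps their data up to that point. It does not mention patients who develop an exclusion criterion after allocation.

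**The concern.** An exclusion criterion is a screening rule: it should describe something that can be established before the patient is assigned. This one describes an event that has not yet happened when eligibility is checked. Under the stated sequence it works as a rule for removing randomised patients, while the analysis commitments require that they be kept. Site staff and the analyst could each follow the protocol and reach different analysis sets.

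Two things are at stake. First, comparability of the arms: one arm is given three upper-limb exercises (wall push-up, shoulder extension, shoulder external rotation) and the other is not, so upper-limb injuries need not occur equally often in both. Removing them could make the arms differ for reasons connected with treatment. Second, numbers: in a trial of 32, each exclusion draws on a reserve already earmarked for ordinary attrition.

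**Working it through.** **1. Order of events, from the protocol's own sections**

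| Step | Time | Section |
|---|---|---|
| Eligibility check, consent | Before surgery | Eligibility; Study Design |
| Baseline test (T1) | Pre-operative, within 14 days | Data Collection |
| Envelope opened | After T1 | Randomisation and Allocation |
| Surgery | Week 0 | – |
| Limb injury after surgery can first occur | From week 0 | Inclusion/Exclusion Criteria |
| ULIT taught | Week 4 | Intervention Group |
| Primary change measured | Weeks 4 to 12 | Statistical Analysis |

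The excluded event falls below the allocation row, so no patient can meet the criterion before randomisation. No single sentence says that the envelope is opened before surgery; this follows from reading Study Design, Randomisation and Allocation, and Data Collection together. If the Abstract were taken literally and allocation came soon after surgery, injuries in the remaining weeks up to week 12 would still follow allocation.

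**2. The two instructions side by side**

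The exclusion list, read in its ordinary sense, says that such a patient is not in the study. Intervention Fidelity, Blinding and Statistical Analysis say that patients are analysed as allocated. Withdrawal from Trial does not settle the matter, because it covers withdrawn consent only.

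**3. The reserve in the sample size**

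Inputs from Sample Size: 14 per group required, 10% attrition, SD 0.71, power 80%, type I error 0.05. Statistical Analysis makes the tests two-sided.

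- Reproducing the plan's figure: 14 / (1 − 0.10) = 15.6, rounded up to 16 per group, 32 in total. This agrees with the protocol.
- Reserve: 32 − 28 = 4 patients, or two per arm, all of it assigned to attrition.

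The protocol gives no rate for these injuries. Assume that a proportion p is excluded, with 10% attrition on top. The number remaining is 32 × (1 − p) × 0.9:

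| Assumed p | Excluded (32p) | Remaining | Required |
|---|---|---|---|
| 3% | 1.0 | 27.9 | 28 |
| 5% | 1.6 | 27.4 | 28 |
| 10% | 3.2 | 25.9 | 28 |

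**4. What that does to power**

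The protocol states no between-group difference, so I solved for the one that gives 80% power with 14 per group at SD 0.71. The normal formula gives (1.96 + 0.84) × 0.71 × √(2/14) = 0.75; the two-sample t-test gives 0.78. Taking 0.78, with noncentrality 0.78 / (0.71 × √(2/n)) and 2n − 2 degrees of freedom:

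| n per arm | Power |
|---|---|
| 16 | 85% |
| 14 | 80% |
| 13 | 77% |
| 12 | 73% |

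The loss of power is modest. The main problem is which patients are lost.

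**The case against.** The best defence is that nothing in the protocol says an injured patient leaves follow-up or the analysis. Intention-to-treat is stated three times, and deviations are to be documented. That stands: the removal follows from listing the event as an exclusion and is not expressly directed. It makes the defect an unresolved contradiction rather than a declared plan to drop patients, but it does not resolve it.

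A reader might infer more, and the documents do not support it:

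- **That harm would be concealed.** Adverse events has them collected by questionnaire throughout the intervention phase, passed to the principal investigator daily, and published whatever the result.
- **That patients would be lost from the ULIT arm only.** The criterion applies to both arms and also names the contralateral lower limb. Unequal loss is a reasoned risk. Any figure for the resulting bias would need the number excluded, their arm and their hamstring strength, none of which is given.
- **That the week-4 value is contaminated.** After the envelope is opened, "Subsequently, they notify the group assignment to the attending physiotherapist", but five physiotherapists give standard care and a single one gives ULIT, and the text does not say which is told. Strength is tested by blinded assessors away from the physiotherapy unit, and nothing shows that care would differ before week 4.
- **That graft and ligament criteria have the same fault.** Inclusion rests on the planned graft and is checked from records and the surgeon's examination. The section does not say that these are settled only at operation.
- **That allocating before surgery is an error.** It is not wrong in itself.

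**Conclusion.** The point holds as a conflict within the protocol. A listed exclusion can arise only after randomisation, the analysis sections require randomised patients to be kept, and no section says which governs. It rests on two readings: that allocation is pre-operative, which three sections together support and only the Abstract's wording does not fit, and that an exclusion criterion carries its ordinary meaning.

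The size of any bias cannot be stated from the documents. On numbers, the reserve is two patients per arm. Under assumed exclusion rates of 3% to 10%, the expected total remaining is 27.9 down to 25.9 against 28, and power at the implied difference would be 77% with 13 per arm. The correction is warranted mainly because the rule could select patients out of a 32-patient trial after assignment, possibly unequally by arm, and because it is so easily removed.

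**What to change.** 1. In Inclusion/Exclusion Criteria, keep only conditions that can be verified before the envelope is opened, and delete limb injury after surgery.
2. State that a limb injury after allocation is recorded through the existing adverse-event process, and that the patient stays in follow-up and is analysed in the allocated group. One sentence in Withdrawal from Trial would separate this from withdrawn consent.
3. Reword the Abstract so that its description of who is randomised agrees with Study Design, Randomisation and Allocation, and Data Collection.

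The cost is a short wording amendment, with no added visits, measurements or patients.

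Opening the envelope only just before ULIT starts is an optional alternative, not part of this correction. It would let events up to that point be screened, but it is more than a wording change. The week-4 assessment has a window of ±14 days, so allocation after that test could fall as late as about week 6, whereas ULIT is set for the fourth week. Those provisions would have to be reconciled first.

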### **Recruitment Feasibility**

Our objective is to enrol 32 individuals from the list of ACLR elective surgical patients at the HCTM using an ipsilateral Hamstring autograft. Hence, the anticipated duration for recruiting 32 individuals is 14 months, with an average of 3-4 ACLR cases per month.

## **Randomisation and Allocation**

Following the baseline assessments, individuals will be assigned either to the intervention group or the control group by a simple random sampling. The randomisation process will be performed using a computer-generated sequence numbering scheme ranging from one (1) to thirty-two (32), with an equal allocation ratio of 1:1. The concealment is achieved using a set of sealed and numbered envelopes. Allocation takes place following baseline testing (T1), when a staff of the Orthopaedic Department, who is not participating in the study, opens the next study envelope. Subsequently, they notify the group assignment to the attending physiotherapist. The envelopes will be securely stored and sealed in a cabinet to ensure security and prevent any unauthorised access. Measures will be implemented to restrict the number of authorised individuals who have access or authority to open the research envelopes, to prevent any potential bias in the allocation process. The statistical analysis will specifically focus on allocation codes, ensuring that the data analyzers remain unaware of the study group allocation (see Figure 9).

[figure not shown]

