**Figure 9: Study Three (RCT) Flow Chart**

### Control group (Standard care)

Patients will be directed to follow the standard care ACLR rehabilitation protocol from preoperative until 12 weeks after the ACLR (see Figure 10). Both study groups will receive standard physiotherapy care from the Department of Medical Rehabilitation Services (HCTM). For standard care rehabilitation sessions, there are five physiotherapists in charge with more than five years of clinical expertise in musculoskeletal rehabilitation. Current rehabilitation strategies consist of knee mobilisation exercises, cryotherapy, and progressive resistance exercises, including eccentric strengthening exercises, proprioceptive training, and dynamic stabilisation drills. The standard outpatient physiotherapy program takes about one hour per session, with a recommendation of 1-2 sessions per week until three months post-operative.

All participants are encouraged to diligently follow the designated daily home exercise program. The standard care involves a personalised therapeutic exercise programme that is specifically designed to meet the needs of each client's goal and the timeline of ACLR recovery. This physiotherapy outpatient rehabilitation program lasts approximately one hour per session, with 1-2 attended sessions per week recommended until three months post-operative. Furthermore, all participants are instructed to diligently adhere to the prescribed daily home exercise programme (see Appendix H).

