### **Intervention Fidelity**

A physiotherapist will conduct follow-up phone calls to evaluate exercise adherence for both groups. They will use standardized guidelines and handouts to encourage patients' exercise adherence, minimizing biases. A flexible and patient-centred approach is applied to address a patient's deviation from their rehabilitation protocol. This involves assessing and reevaluating the patient's progress, modifying the rehab plan for individual needs, rescheduling missed sessions, maintaining weekly communication (online exercise diary), documenting changes and analysing data under an intention-to-treat (ITT) protocol to reduce bias and preserve randomisation.

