### **Adherence monitoring**

A threshold for adherence is established for the experimental group, targeting participants to report a self-perceived rating of  $\geq 80\%$  (Cimino & Braun, 2023). Participants are advised to adhere to the instructions on home-based programs included in their respective flyers. The study used self-report scales and exercise diaries to measure adherence to the home exercise programme over 3 months. Participants are classified as adhered ( $\geq 3$  times per week) or non-adhered ( $\leq 2$  times per week) based on the average frequency of sessions performed weekly (Welling, 2024). Participants are instructed to complete the weekly exercise diary via online Google Form (see Appendix J). Physiotherapists will contact participants weekly via phone or WhatsApp to reinforce their exercise adherence. Self-report questionnaires and activity diaries have demonstrated efficacy, simplicity, and affordability as means of assessing exercise adherence in clinical and research contexts (Lahham et al., 2018; Nicolson et al., 2018).

The Sports Injury Rehabilitation Adherence Scale (SIRAS) is administered by a physician and physiotherapist to assess the level of adherence of all patients to the rehabilitation procedure in both study groups at the Orthopaedic Clinic and physiotherapy outpatient rehabilitation session (see Appendix E). The SIRAS is a reliable measure for evaluating clinic-based adherence in musculoskeletal rehabilitation with inter-rater and test-retest reliability coefficients ranging from 0.76 to 0.93 (Furlong & Hall, 2023).

ACL rehabilitation adherence and recovery can be significantly impacted by fear of movement, addressed by the Tampa Scale of Kinesophobia (TSK), a self-report checklist, utilising a 4-point likert scale (Ohji et al., 2022). By monitoring this fear, clinicians can improve compliance and modify rehabilitation programs (Kasmi et al., 2023). The TSK enables personalised treatment to overcome physical and psychological barriers. The TSK will be assessed preoperatively and at 3 months post-ACL reconstruction to monitor changes in fear of movement and reinjury (see Appendix F). The Tampa Scale of Kinesophobia (TSK) is available online for free use at <https://eprovide.mapi-trust.org/instruments/tampa-scale-for-kinesiophobia-11>, requiring only proper citation and acknowledgement in relevant publications or research (Woby et al., 2005).

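### The allocation goes to an undefined attending physiotherapist weeks before ULIT starts, and all physiotherapists are treated as unblinded, so the adjustable standard care shared by both arms could come to differ by arm

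*Protocol*

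**What the plan says.** All references are to the protocol.

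- **Randomisation and Allocation.** Allocation follows the baseline tests. An uninvolved member of the Orthopaedic Department opens the next envelope, and "Subsequently, they notify the group assignment to the attending physiotherapist". The role is not defined further.
- **Data Collection.** Baseline is pre-operative, within 14 days.
- **Control group (Standard care).** "Both study groups will receive standard physiotherapy care from the Department of Medical Rehabilitation Services". "For standard care rehabilitation sessions, there are five physiotherapists in charge". The content includes progressive resistance and eccentric strengthening, at a recommended 1-2 one-hour sessions a week up to three months. It is individual: "The standard care involves a personalised therapeutic exercise programme that is specifically designed to meet the needs of each client's goal".
- **Intervention Group.** "A single physiotherapist will administer the ULIT", in one personal session in the fourth post-operative week. Patients then do the exercises daily, as a warm-up and at home, for eight weeks.
- **Intervention Fidelity.** Departures from the rehabilitation protocol are handled flexibly, including "modifying the rehab plan for individual needs, rescheduling missed sessions". Changes are documented and the analysis is by intention-to-treat.
- **Blinding.** Because of the nature of the treatments, "it will not be possible for physiotherapists to be blinded to the treatment allocation of patients". Patients are reminded not to disclose their group, but only to those who assess outcomes. ULIT details stay out of the medical record, and a code break is available when a patient's care requires it.
- **Adherence monitoring.** "A threshold for adherence is established for the experimental group", at 80% or more on a self-rating. Physiotherapists contact participants weekly to reinforce adherence.

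**The concern.** The research question is whether ULIT adds something to standard care. The arm comparison answers it only if the standard care is the same in both arms apart from ULIT. Here the shared care is discretionary in content and frequency, includes strengthening that can act directly on the endpoint, and is delivered by staff whom the protocol treats as aware of the arm. If awareness changes how they progress, schedule or encourage the shared programme, the difference between arms is part ULIT and part unequal hamstring training. Such a difference in strength would be real, so blinded assessors would measure it faithfully and intention-to-treat would carry it into the estimate.

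The reason given for not blinding, the nature of the treatments, fits the person who teaches ULIT. The protocol does not explain why colleagues who deliver only the shared programme need to be told the arm.

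**Working it through.** The point rests on no figure in the plan, so there is none to reproduce. The check is a reading of the sections together, followed by an illustration of scale.

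**1. Who needs the allocation, and when**

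| Task | Who, per protocol | Needs the arm? |
|---|---|---|
| Teach ULIT, week 4, one session | One physiotherapist | Yes, from week 4 |
| Deliver standard care, both arms | Five physiotherapists | No reason stated |
| Weekly adherence contact | Physiotherapists | For ULIT questions only |

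Allocation follows a baseline taken up to 14 days before surgery, and ULIT starts 4 weeks after surgery. Notice is therefore given about 4 weeks (0 + 4) to 6 weeks (2 + 4) before anyone needs it.

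**2. Room for the shared care to vary**

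12 weeks x 1 to 2 one-hour sessions = 12 to 24 supervised hours. This range is recommended for every patient. It shows how much discretion exists; it is not a difference between arms.

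**3. Safeguards in place**

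- A half-day workshop for assessors and treating physiotherapists (Blinding).
- Standardised guidelines and handouts for adherence calls in both groups, and documentation of changes (Intervention Fidelity).
- Exercise diaries, and the Sports Injury Rehabilitation Adherence Scale (SIRAS) in both groups (Adherence monitoring).

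These bear mainly on adherence and record-keeping. In the text available, nothing says how supervised content is kept alike across arms or plans a comparison by arm of the standard care delivered.

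**4. Illustration of scale (assumption, not a finding)**

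In the table under Sample Size, involved-limb hamstring torque rises from 1.0 at week 4 to 1.55 Nm/kg at week 12: 1.55 - 1.0 = 0.55. Suppose that unequal standard care changed this recovery by 10-20%, a range with no source in the protocol:

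- 0.10 x 0.55 = 0.055 Nm/kg; 0.20 x 0.55 = 0.11 Nm/kg.
- Against the planning SD of 0.71: 0.055/0.71 = 0.08 SD; 0.11/0.71 = 0.15 SD. The protocol attaches this SD to the symmetry index, so reading it on the torque scale is a further assumption.

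With no true ULIT effect, the chance of a significant two-sided 5% t-test under a spurious mean shift d comes from the noncentral t distribution, with df = 2n - 2 and noncentrality (d/0.71) x sqrt(n/2). For d = 0.1 and n = 14: 0.141 x 2.646 = 0.373, df = 26, critical value 2.056.

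| Shift d | 14 per arm | 16 per arm |
|---|---|---|
| 0 | 5% | 5% |
| 0.055 | 5.4% | 5.5% |
| 0.1 | 6.5% | 6.7% |
| 0.11 | 6.8% | 7.1% |
| 0.2 | 11% | 12% |
| 0.3 | 19% | 21% |

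Within the assumed 0.055-0.11, the rise in false positives is modest. The last two rows show what larger shifts would do; the protocol gives no basis for choosing among them.

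**The case against.** **The text may mean something narrower.** The attending physiotherapist is singular and undefined, and may simply be the one who teaches ULIT and must know the arm. A reader might infer that ULIT is given by someone separate from the five, or that all five are notified. The protocol supports neither: it says one physiotherapist, not a separate one, and that person could be among the five. The point survives either reading, because Blinding treats physiotherapists as a whole as unblinded and the notice is weeks early in any case.

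**Standardisation may exist where it cannot be seen.** The standard-care figure and the home-programme appendix are not available here, so how tightly progression is fixed cannot be judged. This stands, and it is one reason why the size is left unknown.

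**Coaching need not favour one arm.** One might infer from the experimental-arm adherence target that weekly contacts push one way. No section tells callers to treat the arms differently, and Intervention Fidelity describes standardised guidelines for both groups. What remains is that the 80% target is set for one arm only.

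**Early knowledge falls before the measured window.** Statistical Analysis defines the main outcome as change from week 4 to week 12. Drift before week 4 therefore acts on the starting value, at least in part. Drift after week 4 acts on the change itself.

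**This is a disclosed, pragmatic design.** Unblinded therapists and personalised usual care are openly declared, and Duration and Timeline plans pragmatic-trial reporting. That makes the choice defensible, but it does not explain why staff who give only the shared care should be told the arm.

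**Blinding these staff will leak.** Patients talk, and ULIT is used as a warm-up. This stands: the gain is a partial blind.

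**Conclusion.** The concern holds as a risk of performance bias that the protocol could reduce cheaply. It is not a demonstrated bias. The allocation is released 4 to about 6 weeks before ULIT begins, to a recipient who is not identified. The shared standard care is adjustable, includes strengthening relevant to the endpoint, and is given by staff declared unblinded. The existing safeguards lessen the risk but would neither prevent nor clearly reveal a difference in supervised care between arms.

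The size cannot be derived from the documents. The 0.055-0.11 Nm/kg figure depends wholly on the assumed 10-20% and should not be cited as an expected bias. The conclusion rests on two assumptions: that some standard-care physiotherapists would not otherwise know the arm, and that those who do know could act on it. This is a recommended improvement, not a defect that invalidates the trial.

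**What to change.** 1. **Randomisation and Allocation.** State that only the physiotherapist who teaches ULIT is notified, and only when the week-4 session is due, after the week-4 assessment. That assessment has a window of plus or minus 14 days, so the order of the two should be written down. Do not routinely send the allocation to the standard-care physiotherapists.
2. **Intervention Group.** Say whether the ULIT physiotherapist is one of the five. If so, that person should, where rostering allows, not give standard care to trial patients.
3. **Blinding.** Limit the statement that blinding is impossible to the ULIT physiotherapist. Extend the existing reminder not to reveal the group to standard-care sessions. Keep the existing code break for patient care.
4. **Recording.** Log attended sessions and hamstring-specific standard-care content for both arms, and report them by arm.
5. **Adherence monitoring.** Apply the same adherence criterion for the shared home programme in both arms, and ask about ULIT adherence separately.

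How ULIT itself is delivered, and who makes the weekly contacts, can stay as planned.

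Cost: protocol wording, a changed notification route and a short session log, with no extra staff. The downside is an imperfect blind, because patients may disclose their group and ULIT is used as a warm-up. The record by arm is useful even where the blind fails, since it would show any drift in the items logged.
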